### Women’s incentives

SAM and MAM programmes have been operational in the Zinder region for 15 years, and RUTF/RUSF are regularly found for sale in markets. During the OptiMA Mirriah pilot non-comparative cohort study, women refused to participate in the study to integrate the standard protocol and receive a maximum dose of RUTF/RUSF (personal communication, 2020). To ensure that the trial is understood, accepted, and implemented in accordance with local customs and practices, meetings to explain the trial eligibility and procedures were organised with community representatives and with nutrition actors. During the trial’s active phase, regular oral presentations are held at the local level. Neither monetary nor financial incentives to compensate for the loss of dose reduction were offered, but soaps were given to caretakers especially those randomised in intervention arms at inclusion, at the end of outpatient follow-up, and at the exit of the trial to increase their adherence to the trial.

### Data collection and management

Data are collected using the national programme individual outpatient cards that were modified to include specific clinical and follow-up data. Additional paper forms are also completed to collect demographic and economic data. Clinical trial technicians are based at each of the four health facilities to ensure the consent process, enrolment, randomisation, and dosage quantities according to the trial’s SOP. They also assess the accuracy of anthropometric measurements taken by the health facility staff and the medical visit by the nurses. Randomisation is realised using a specific offline tool developed especially for the study by our partner PACCI, for a branch for the French National Agency for Research on AIDS and Viral Hepatitis in Abidjan, Côte d’Ivoire. Data collected on paper forms are entered by data clerk agents based on each site and supervised by a data manager, using the RedCAP software from the offline tablet.

Monitoring is ensured by two clinical trial monitors under the responsibility of the research field coordinator and his deputy based in Zinder, in compliance with the recommendations of Good Clinical Practice. All data and any adverse events, including deaths and hospitalisations, are rigorously monitored weekly both on-site and remotely, according to the data monitoring plan. To ensure patient safety and data integrity, the methodology and coordinating centre continuously supervised data management activities, and the senior scientific project leader and investigators performed field visits on a regular basis.

### Statistical analysis

All statistical analyses will be performed using the RStudio Software (Boston, MA, USA) as specified by the data analysis plan published on ClinicalTrials.gov prior to performing any analysis. Statistical tests will be carried out bilaterally with an alpha risk of 5% and unilaterally with an alpha risk of 1.25% for the non-inferiority analysis. Qualitative variables will be described in terms of numbers and percentages and provided with CIs when relevant. If necessary, comparisons of qualitative variables will be made using *χ*^2^ or Fisher exact tests. Quantitative variables will be described in terms of mean, SD, and CI or median, range, and IQR. If necessary, comparisons of quantitative variables will be made using Student’s, Wilcoxon’s, or Kruskal-Wallis tests, depending on the distribution of the variable of interest. Time delay type variables will be described in terms of the incidence of occurrence, and the probability of occurrence over time, estimated by the Kaplan-Meier method. If necessary, probability comparisons will be made using log-rank tests, or proportional risk models, after verification of the assumption of proportionality of risks.

The main analysis of the primary and secondary outcomes will be intention-to-treat and per-protocol given that this is a non-inferiority trial. Participants included in the main analyses will be described according to the diagram defined by CONSORT (Consolidated Standards of Reporting Trials) recommendations [18]. The occurrence of the primary “favourable outcome” and the secondary main outcome “recovery” will be compared between the two randomisation arms. These two comparisons will be performed both by “intention-to-treat” basis and on a “per-protocol” basis. Non-inferiority analyses will be performed on these two outcomes. Only if non-inferiority for these two outcomes is demonstrated will the other secondary analyses will be performed and, if appropriate, as a superiority analysis. Superiority will be particularly sought for cost outcomes related to RUTF cost-efficiency.

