The Combined Protocol for Acute malnutrition Study (ComPAS) was developed by the International Rescue Committee (IRC) and consists in reducing the dosage according to the child’s MUAC during the outpatient follow-up and has the simplest dosing regimen ever tested: 2 RUTF sachets/day to children with MUAC < 115 mm or oedema and 1 RUTF sachet/day for children in the 115–124 mm MUAC category [12]. The main advantage of this strategy is that it can be implemented by community health workers, regardless of literacy level and without other anthropometric tools rather than a MUAC tape. Simplification and decentralisation of nutrition programming to the community level stand the best chance of increasing service coverage. A cluster-randomised controlled non-inferiority trial was implemented in Kenya and South Sudan in 2017 and showed that recovery in the ComPAS arm (76.3%) was non-inferior to that of the standard care arm (73.5%): risk difference of 0.03, 95% CI − 0.05 to 0.10, *p =* 0.52 [13]. The average amount of RUTF for SAM children was significantly lower under the ComPAS protocol (122 sachets) compared to the standard one (193 sachets) [13].

These simplified nutrition protocols deviate from existing normative guidance, and despite the MUAC-based common approach, there is currently a lack of consensus on these modifications. More evidence is needed prior to developing such simplified and optimised approaches at scale. Burning issues include which dosage is better to implement and what is the impact of such reduced regimens on recovery, especially among the most vulnerable children (MUAC < 115 mm).

This is exactly what this community-based non-inferiority trial proposes by comparing the OptiMA and ComPAS strategies to the current Niger protocol of AM treatment. We hypothesised that the OptiMA and ComPAS strategies would be as effective as the current Niger national protocol currently in use in children aged 6 to 59 months. This hypothesis will be assessed by reaching a favourable outcome in the treatment of uncomplicated SAM and MAM at 6 months post-randomisation and in terms of recovery rate in the treatment of uncomplicated SAM (WHZ < − 3 or MUAC < 115 mm or oedema) and also among children admitted with MUAC < 115 mm.

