**Main secondary**			
Recovery	Composite: absence of bipedal oedema and a MUAC > 125 mm for two consecutive weeks, a 4-week minimum duration of RUTF treatment, and a good clinical health (without fever)	Proportion	Throughout the 6-month follow-up period
**Secondary**^a^			
Cost-effectiveness	Incremental cost-effectiveness ratio (ICER)	Ratio	Throughout the 6-month follow-up period
Consumption of RUTF per children with a favourable outcome	Sachets of RUTF consumed	Mean	6-month post-inclusion
Consumption of RUTF per recovered children	Sachets of RUTF consumed	Mean	End of RUTF treatment initiated at inclusion
Average daily weight gain in SAM children recovered	g/kg/day	Daily	End of RUTF treatment initiated at inclusion
Average daily MUAC gain in SAM children recovered	mm/day	Daily	End of RUTF treatment initiated at inclusion
Hospitalisation	Children with at least one episode of hospitalisation	Proportion	Throughout the 6-month follow-up period
Relapse to a new episode	Children with MUAC < 125 or WHZ < − 3 *Z*-score or oedema after RUTF treatment	Proportion	After recovering from the first episode of acute malnutrition
Non-response	Children who did not reach the recovery criteria	Proportion	16 weeks after inclusion
WaST	Children associated with severe and moderate stunting with acute malnutrition	Proportion	Throughout the 6-month follow-up period

^a^All the secondary outcomes will be analysed for the overall population (MUAC < 125 mm or WHZ < − 3 or oedema) and for the secondary populations (SAM WHO and MUAC < 115 mm or oedema)

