In the control arm, children included with a MUAC < 115 mm and/or WHZ < − 3 and/or nutritional oedema are treated weekly with RUTF, according to the Niger national protocol dosage table based on the child’s weight. The Niger protocol provides a RUTF daily caloric intake of 150–200 kcal/kg/day during the entire treatment schedule until recovery in children with SAM. Children under 2 years old included with a MUAC between 115 and124 mm and WHZ > − 3 without bipedal oedema are treated weekly by one sachet of RUSF per day (500 kcal/day) during the course of treatment. However, children over 2 years old meeting the same moderate anthropometric criteria are not eligible for supplementation according to the national MAM programme.

The simplified strategies apply to AM children defined as MUAC < 125 mm or bipedal oedema (+, ++) without medical complications on admission and with a good or moderate appetite test.

In contrast to the weight-based RUTF ration in the national SAM programme, the OptiMA RUTF ration is calibrated to the child’s degree of wasting based on the combination of MUAC status and weight. Thus, more nutritional support is given to the most severely malnourished children and then gradually reduced as the child’s MUAC increased. Children with MUAC < 115 mm or oedema receive 175 kcal/kg per day of RUTF. Children with MUAC 115–119 mm, either at admission or during the course of treatment, receive 125 kcal/kg per day of RUTF, and children with MUAC ≥ 120 mm receive 75 kcal/kg per day of RUTF (with a minimum of one sachet/day) until discharge from the programme.

The ComPAS strategy is the most simplified protocol, not requiring a dosage table and proposing to gradually reduce the dosage according to the child’s MUAC status only during the outpatient follow-up as follows: 2 sachets/day of RUTF to children with MUAC < 115 mm or oedema and 1 sachet/day for children in the 115–124 mm MUAC zone.

For both simplified strategies, children with oedema receive the same RUTF ration as children with MUAC < 115 mm until oedema are resolved, at which point their ration is determined by MUAC and weight.

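### RUTF consumption is defined as a mean, but its test may be chosen by the shape of the data; in the overall population a rank test could be significant in the opposite direction to the mean

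*Protocol article*

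**What the plan says.** Table 1 lists two sachet outcomes, "Consumption of RUTF per children with a favourable outcome" and "Consumption of RUTF per recovered children", both with the mean as method of aggregation. Footnote a adds: "All the secondary outcomes will be analysed for the overall population", as well as for the WHO-SAM population and the MUAC < 115 mm or oedema population.

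The Statistical analysis section gives one generic rule for continuous data: where needed, groups are compared with Student's, Wilcoxon's "or Kruskal-Wallis tests, depending on the distribution of the variable of interest". It names no test for sachets specifically. It also says that superiority will be sought above all on cost outcomes tied to RUTF.

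The Intervention section fixes who gets RUTF. In the control arm, non-SAM children under 2 years receive RUSF, and "children over 2 years old meeting the same moderate anthropometric criteria are not eligible for supplementation". In OptiMA and ComPAS the same children receive at least one RUTF sachet a day, and the footnote to Table 3 sets a minimum of 4 weeks.

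**The concern.** The summary is fixed as a mean, but the test is left to the data. In the overall population the control arm mixes non-SAM children at zero with SAM children on the full weight-based ration. No simplified-arm child is at zero by design. A distribution check on such data points naturally to Wilcoxon or Kruskal-Wallis.

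Those tests compare rank order. A simplified-arm child outranks every control child at zero, however few sachets were used, while the control mean is carried by its SAM children. The control arm can therefore have the higher mean and the lower ranks. Product supply depends on total sachets, hence on the mean. A p-value saying that a strategy uses more RUTF, printed beside means saying that it uses less, would confuse programme readers on one of the main arguments for simplification.

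**Working it through.** **Inputs from the article.** Mean sachets per SAM child: 193 standard, 122 ComPAS (Introduction, from the earlier ComPAS trial; used here as assumptions). Control non-SAM: 0. ComPAS non-SAM: one sachet a day for 4 to 16 weeks, so 28 to 112.

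**Assumed, because the article does not give them.** ComPAS non-SAM mean m = 35, 42 or 56; CV of SAM sachets 0.3 or 0.5; SAM share s = 26-70%.

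**Number per arm.** The planned size is reproduced first: 2 × 0.68 × 0.32 × (2.241 + 1.282)² / 0.10² = 540.2, so 541; 541 × 1.05 = 568, as stated in the Sample size section. The simulation uses 541 per arm.

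**Plausible SAM share.** Lower bound: 290/1111 = 26% of pilot children had MUAC < 115 mm, and WHO SAM includes them. Upper bound: pilot recovery was 91% (non-SAM) and 70% (SAM), with more than 80% overall; 91(1 − s) + 70s > 80 gives s < 11/21 = 52%.

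**Where the means cross.** 193s = 122s + m(1 − s), so s = m/(71 + m): 33% for m = 35, 37% for m = 42, 44% for m = 56. Above these shares ComPAS uses less on average.

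**Where the ranks cross.** Zeros never outrank anyone, and a control SAM child nearly always outranks a ComPAS non-SAM child. So P(control > ComPAS) ≈ s(1 − s) + s²a, where a is the chance that a control SAM child outranks a ComPAS SAM child. At s = 45%, m = 42, CV 0.3, the simulated value is 0.421, hence a ≈ 0.857. Setting s − 0.143s² = 0.5 gives s ≈ 54%. With CV 0.5 the simulated value reaches 0.499 at s = 60%.

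Between the two crossings the control arm has the higher mean but the lower ranks.

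**Simulation** (400 runs per setting, two-sided 5%). Percentage of runs with Wilcoxon significant against the direction of the observed means:

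| m, CV | s = 26% | 35% | 40% | 45% | 50% | 55% | 60% |
|---|---|---|---|---|---|---|---|
| 42, 0.3 | 0 | 24 | 71 | 93 | 52 | 2 | 0 |
| 56, 0.3 | 0 | 1 | 14 | 52 | 51 | 3 | 0 |
| 35, 0.5 | 4 | 55 | 90 | 98 | 97 | 48 | 3 |
| 42, 0.5 | 0 | 28 | 69 | 93 | 95 | 52 | 3 |
| 56, 0.5 | 0 | 1 | 14 | 59 | 88 | 62 | 6 |

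At 70% it was 0 in every row. Example: s = 45%, m = 42, CV 0.3 gives means of 86.9 (control) and 78.4 (ComPAS), a saving of 8.5 sachets, with P(control > ComPAS) = 0.42.

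The stricter event, Welch and Wilcoxon both significant in opposite directions, is rarer. For m = 42 it occurs in 37% of runs at s = 45% (CV 0.3) and 64% at s = 50% (CV 0.5); for m = 56 and CV 0.3 it is at most 3%.

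**Loss of sensitivity without reversal.** At s = 60%, m = 42, CV 0.5 the means are 115.8 and 90.2, yet Wilcoxon is significant in only 7% of runs.

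**The case against.** **No test is assigned to sachets.** The rule is conditional, lists Student's test first and gives no normality criterion. With over 500 children per arm an analyst could choose a comparison of means and comply. A reader might infer that the plan prescribes a rank test here; it does not. A reader might also infer that Kruskal-Wallis is the only route for three arms, but two pairwise tests stand beside it. The analysis plan that the article cites is not shown and may settle the matter. This stands, so the point is what the printed rule permits and, on such data, invites.

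**Few outcomes are exposed.** The two SAM populations have no structural zeros. Recovery in Table 1 requires a minimum of RUTF treatment, so read literally a control child who had none drops out of the per-recovered outcome. That leaves mainly consumption per child with a favourable outcome, in the overall population. These secondary analyses also run only if non-inferiority is shown. This stands.

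**That outcome covers fewer children, with a lower SAM share.** At 68% success, 0.68 × 540 ≈ 370 per arm. If success followed pilot recovery (an assumption), s becomes 0.70s/[0.70s + 0.91(1 − s)]: 37%, 45% and 52% become 31%, 39% and 45%. At n = 370 the rank test still contradicted the observed means in 30-85% of trials at 39% and 80-96% at 46%, depending on the inputs; it was small near 31%. So the range shifts but the problem remains.

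**Later enrolment may raise the share.** After the primary sample is complete, only SAM and then MUAC < 115 mm children enter. With 26% of 568 = 148 such children, reaching 384 needs 236 more: (0.37 × 568 + 236)/804 ≈ 56% and (0.52 × 568 + 236)/804 ≈ 66%. If these children count in the overall population, reversal is at most 2% at 58% or more (CV 0.4), and at 66% the rank test reports the saving in 77-90% of trials. This stands.

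**Later RUTF in control children.** If 10% of non-SAM controls later receive a full course (non-SAM mean 50), reversal moves to lower shares: 93% of trials at 37% and 75% at 45%. At 52% it largely disappears, but Wilcoxon finds the saving in 5% of trials against 99% for Welch.

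**Conclusion.** The concern holds in a limited form. The article fixes a mean and then allows a test that does not address it, on data whose zeros come from the design. At SAM shares of about 40-52% a rank test would often contradict the observed means. That range lies within the pilot-implied 26-52%, but the lower end of the pilot range and the shares that extended enrolment could produce are largely free of reversal.

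The percentages rest on ComPAS figures from another trial and on assumed non-SAM use, spread and SAM share; OptiMA was not modelled. It would go too far to say that ranks and means will disagree in this trial, or that a rank test could never show a saving: both depend on a SAM share that the article does not give. Nor is the cost-effectiveness conclusion undermined, because the incremental ratio does not depend on this test. The primary non-inferiority test is unaffected. The mismatch is worth correcting because the correction is nearly free.

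**What to change.** Add one sentence to the statistical analysis section or the analysis plan: RUTF consumption, and any cost outcome summarised as a mean, is compared pairwise with the standard arm as a difference in arithmetic means, with a Welch or bootstrap confidence interval, whatever the distribution; rank tests are descriptive only. It is also worth stating whether children enrolled after the primary sample is complete count in the overall population for this outcome, since that sets the SAM share. No new data, visits or sample size are needed.

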## Objectives

The principal objective aims to determine, 6 months after inclusion, whether the OptiMA strategy or ComPAS strategy leads to a favourable outcome which is non-inferior to what Niger standard protocol, in use in the same outpatient health facilities, provides. The definition of a favourable outcome is described in the “Study outcomes” section.

Two main secondary objectives for this trial are as follows. The first one is to determine whether the recovery rate of children with uncomplicated SAM according to the current WHO definition [14] (e.g. MUAC < 115 mm or WHZ < − 3 or bilateral oedema) managed under the simplified OptiMA or ComPAS strategies is non-inferior to that of the national standard protocol of Niger. The second one is to determine whether the recovery rate of children admitted with MUAC < 115 mm or oedema (+, ++) managed under the simplified OptiMA or ComPAS strategies is non-inferior to that of the national standard protocol of Niger.

Other secondary objectives include description and comparison between the three study arms of the following outcomes: cost-effectiveness analysis, RUTF consumption, relapse after nutritional recovery, non-response after outpatient follow-up, recovery, and success in children who present with both wasting and stunting at inclusion, and to describe the nutritional and clinical status of children hospitalised while enrolled in the study.

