### Trial design and study period

This study is a non-inferiority individually randomised controlled clinical trial conducted at the health centre level and in the community. Participants are randomly assigned to either the OptiMA or ComPAS strategy arms (intervention = OptiMA or ComPAS) or the national standard protocol arm (control = standard). Inclusions started on March 23, 2021, for a 9-month period with an expected end in December 2021. All participants are followed for a 6-month period post-randomisation, with an active phase expected to end in June 2022.

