### Study outcomes

The primary outcome will be judged by a binary composite indicator. Children classified as “favourable outcome” fulfil all of the following criteria: alive, not acutely malnourished per the anthropometric definition applied at inclusion (MUAC > 125mm and WHZ > − 3, and no oedema) and not having an additional episode of AM throughout the 6-month observation period. This outcome is measured at 6 months after randomisation. All other children are classified as “unfavourable outcome”.

The main secondary outcome #1 will be determined among children who meet the current WHO definition of SAM at inclusion (MUAC < 115 mm or WHZ < − 3 or oedema +, ++). The main secondary outcome #2 will be determined among children admitted with a MUAC < 115mm or oedema (+, ++). For these two subgroups, recovery is defined in each arm by a 4-week minimum duration of treatment, an axillary temperature < 37.5 °C, and an absence of bipedal oedema and a MUAC ≥ 125 mm for two consecutive weeks. This outcome is measured throughout the 6 months post-randomisation, meaning a child will be considered as recovered if he reaches these criteria during the 6-month follow-up in outpatient or village visits. Additional secondary outcomes are listed in Table 1.

**Table 1 Tab1:** Primary and secondary outcomes in the OptiMA Niger trial

	Measurement variable	Method of aggregation	Time point

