### Safety

The trial is monitored monthly by an international steering committee and twice a year by a national steering committee where any adverse events are presented. We also planned a field visit by the national steering committee during the enrolment phase. The data safety and monitoring board (DSMB) for this trial did not request any interim analysis, but security analyses are planned after 500 and 1500 inclusions and will consist in comparing across study arms mortality, hospitalisation, and life-threatening events rates. The DSMB will meet at least twice during the recruitment phase to make recommendations following the security analysis. The ethics committees did not require any meetings during the active phase.

A child included in one of the two intervention arms could be removed from the study if (s)he experiences two consecutive episodes of > 5% weight loss during the course of treatment and is hospitalised once, or if (s)he is not SAM at inclusion but deteriorates to SAM during RUTF supplementation.

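### The statistical section performs the other secondary analyses only if non-inferiority is shown, contradicting Table 1 and withholding the final hospitalisation comparison when it is most needed

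*Protocol article*

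**What the plan says.** The Statistical analysis section names two outcomes for non-inferiority testing, favourable outcome (primary) and recovery (main secondary). It then sets the rule: "Only if non-inferiority for these two outcomes is demonstrated will the other secondary analyses will be performed". The sentence goes on to allow a superiority analysis where appropriate.

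Other parts of the article set no such condition:

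- Table 1, footnote a: "All the secondary outcomes will be analysed for the overall population", and also for the two severe populations. Relapse, 16-week non-response and hospitalisation ("Children with at least one episode of hospitalisation", over the 6-month follow-up) are all in the table.
- Objectives: "Other secondary objectives include description and comparison between the three study arms of the following outcomes". The list includes relapse and non-response. For hospitalised children it promises only a description of their status.
- The Statistical analysis section itself: the main analysis of both primary and secondary outcomes is to be by intention to treat and per protocol.

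Some information on harm sits outside the gate. The primary composite requires a child to be "alive, not acutely malnourished per the anthropometric definition applied at inclusion" and free of further episodes. The general reporting rule is also unconditional: "Qualitative variables will be described in terms of numbers and percentages and provided with CIs when relevant". Under Safety, "security analyses are planned after 500 and 1500 inclusions and will consist in comparing across study arms mortality, hospitalisation, and life-threatening events rates".

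**The concern.** A gate is a sound way to order confirmatory claims. Here, as worded, it decides whether the secondary analyses are done at all. An analyst who follows the Statistical analysis section stops after a failed non-inferiority test, while one who follows footnote a carries on. The article supports both.

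Wrong adoption of a reduced ration is not at stake, because the Discussion already says that dose reduction would not be advisable if non-inferiority fails. The loss is in interpretation. When a reduced ration misses non-inferiority, readers need to know whether the estimate was merely imprecise or came with more hospitalisation, relapse or non-response. The rule withholds those final comparisons in exactly that case.

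**Working it through.** **1. Which outcomes the gate removes.**

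| Outcome | In an ungated outcome? | If the gate closes |
|---|---|---|
| Death | Yes, in the primary composite | Counted, but not compared separately |
| Further episode or relapse | Yes, in the primary composite | Counted, but not compared separately |
| 16-week non-response | Partly, mirrors recovery | Not compared separately |
| 6-month hospitalisation | No | No final between-arm comparison |

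**2. The plan's own sample sizes.** Inputs from Sample size and Statistical analysis: margin 0.10; one-sided alpha 1.25% (z = 2.241); power 90% for the primary and 80% for the main secondary objectives; expected rates 68%, 82% (SAM) and 74% (MUAC < 115 mm or oedema); 5% inflation.

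n = (z_alpha + z_power)² × 2p(1 − p) / 0.10² gives 540.1, 280.6 and 365.8 evaluable per arm. Divided by 0.95 these are 568.6, 295.4 and 385.0, within about one child of the stated 568, 295 and 384. The steps below use 540, 280 and 365.

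**3. How often the gate closes for one strategy.** With a true deficit d and pt = pc − d:

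P(pass) = Φ((0.10 − d)/SE − 2.241), SE = √(pc(1 − pc)/n + pt(1 − pt)/n).

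Example, favourable outcome at d = 0: SE = √(2 × 0.68 × 0.32/540) = 0.0284; 0.10/0.0284 − 2.241 = 1.281; Φ = 0.900.

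| True deficit on both outcomes | Favourable (68%, 540) | Recovery, MUAC < 115 mm (74%, 365) | Recovery, SAM (82%, 280) |
|---|---|---|---|
| 0 | 0.900 | 0.799 | 0.799 |
| 3 points | 0.578 | 0.451 | 0.441 |
| 5 points | 0.305 | 0.229 | 0.220 |

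The correlation between the two outcomes is not given, so a range is shown. Under perfect positive dependence P(closed) = 1 − min(a, b); under independence it is 1 − ab. With favourable outcome and recovery in MUAC < 115 mm:

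| Deficit | Perfect dependence | r = 0.6 | r = 0.3 | Independence |
|---|---|---|---|---|
| 0 | 0.201 | 0.241 | 0.264 | 0.281 |
| 3 points | 0.549 | 0.641 | 0.692 | 0.739 |
| 5 points | 0.771 | 0.856 | 0.896 | 0.930 |

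Using SAM recovery instead gives 0.201–0.281, 0.559–0.745 and 0.780–0.933. With no unexploitable data (568 and 384 per arm) and equal arms the range is 0.179–0.249.

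Stricter readings close it more often. With equal arms and independent outcomes, requiring both recovery populations gives 1 − 0.900 × 0.799 × 0.799 = 0.43 for one strategy. Requiring both strategies to pass as well (correlation 0.5 from the shared control) gives 1 − 0.832 × 0.686 × 0.686 = 0.61.

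**4. What the last safety look would cover.** Trial design and study period plans inclusions "for a 9-month period with an expected end in December 2021". Assume 3 × 568 = 1704 children accrued evenly:

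- 1704/9 = 189.3 per month, so the 1500th child enters at 7.92 months.
- Children with a full 6 months: 189.3 × 1.92 = 364, or 21% of 1704.
- Person-months observed: 364 × 6 + 1136 × 3 = 5592, of 1704 × 6 = 10224 planned, or 55%.

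If July–October accrual is 2 to 3 times that of other months, coverage is 47% to 39%. If continued enrolment of SAM children takes the total to 1900–2100 with even accrual, it is 46% to 38%.

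**5. Whether a final comparison would be informative.** The article gives no hospitalisation rate, so rates are assumed. At 568 per arm the 95% half-width, 1.96 × √((p1(1 − p1) + p2(1 − p2))/568), is 3.1 points for 5% v 10%, 3.8 for 10% v 15% and 4.4 for 15% v 20%. In each case a 5-point difference exceeds the half-width.

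**The case against.** The strongest reply is that only a testing hierarchy was meant. The sentence follows the non-inferiority analyses, mentions superiority, and is followed by a remark that superiority will be sought for cost outcomes. It is also ungrammatical, and the registered analysis plan, not shown here, may limit it to tests. That may well be the intent. As written, though, it governs whether the analyses are performed and adds superiority separately. The unconditional statement about the main analysis in the same section is one more text that it contradicts.

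Second, the direct conflict on hospitalisation is narrower than it may appear. The Objectives promise no comparison of hospitalisation rates, and footnote a is mainly about populations. This stands in part: the hospitalisation point rests on Table 1 and its footnote alone. The footnote still says that all secondary outcomes will be analysed.

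Third, little would be lost, because percentages can be reported unconditionally and a reader could compute a risk difference from the counts. That limits the damage, but a comparison left to readers is not a planned analysis.

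Fourth, safety is followed outside the gate through weekly monitoring, the steering committees and the DSMB. Over the first 16 weeks of each child's follow-up, the maximum treatment period for a first episode, the 1500-inclusion look would cover about 67% with even accrual. These points are correct, but those looks serve DSMB recommendations during recruitment and are not a final 6-month comparison.

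Finally, the closing probabilities measure how often the rule applies, not the size of any harm. That is conceded.

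**Conclusion.** The concern holds. The article contains a stated rule that contradicts Table 1 and the Objectives. Followed literally, it removes the final between-arm comparisons of hospitalisation, relapse and non-response whenever non-inferiority is missed on either outcome.

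For one strategy and one recovery population, that happens in about 20% to 28% of trials with truly equal arms, 55% to 74% with a 3-point deficit and 77% to 93% with a 5-point deficit. These figures rest on the plan's expected rates, 5% unexploitable data, equal deficits on both outcomes, a normal approximation, and dependence anywhere from independence to perfect positive. The 55% coverage of the 1500-inclusion look also assumes even accrual of 1704 children.

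No data are lost and no wrong adoption decision follows. The point should be corrected, but it does not threaten the primary analysis.

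**What to change.** Replace the gate sentence with one limited to superiority, for example: *Superiority for RUTF use and cost will be tested only if non-inferiority has been shown for favourable outcome and recovery.*

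Then state that hospitalisation, relapse, non-response and all-cause death by 6 months are reported by assigned arm whatever the non-inferiority result. Each should be a risk difference of each strategy against the national protocol with a 95% confidence interval, labelled descriptive, overall and in the SAM and MUAC < 115 mm or oedema populations. The Statistical analysis section then agrees with footnote a and the Objectives.

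The cost is a short wording change, with no new data and no change to sample size or alpha. The downside is that these intervals carry no multiplicity control and cannot support confirmatory claims.
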